### Allocation and randomisation

After obtaining informed consent, patients will undergo randomisation with stratification for World Federation of Neurosurgical Societies (WFNS) score. Five strata were defined, one for each WFNS score. Within each stratum, separate randomisations are performed between the intervention and control group to ensure a balanced randomisation based on disease severity. This is particularly important because, in patients with high-grade WFNS scores, goals of care may shift toward comfort-focused measures, which can independently affect mortality outcomes regardless of the intervention. Stratification by WFNS grade helps mitigate this potential source of bias. Randomisation is conducted using a web-based permuted block system and performed by the principal investigator or executive researcher. This system employs permuted blocks of variable sizes, ranging from two to six patients, to minimise the predictability of group allocation and ensure balanced sample sizes in each study arm. Patients are randomised in a 1:1 ratio and assigned to one of the two treatment arms.

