### Outcomes

The primary objective is to evaluate whether treatment with high-dose LMWH in patients with coiled aSAH significantly reduces mortality assessed at 30 days after the initial bleeding. Secondary objectives are to evaluate whether this treatment significantly reduces the presence and severity of DCI (measured by the Modified National Institutes of Health Stroke Scale),^29^ increases the incidence of major bleeding (defined as a fatal bleeding and/or symptomatic bleeding in critical areas or organs (such as intracranial, intraspinal, intraocular, retroperitoneal, intra-articular, pericardial or intramuscular bleeding causing compartment syndrome) and/or bleeding resulting in a haemoglobin drop of 1.2 mmol/L or more, or requiring a transfusion of two or more units of whole blood or red cells) and non-major bleeding (defined as all reported bleedings not classified as major),^30^ increases the risk of haemorrhagic complications after shunt placement or lumbar puncture, reduces other SAH-related complications (such as severe hyponatraemia, postprocedural aneurysm rupture, rebleeding, delirium, epilepsy, diffuse parenchymal swelling or nosocomial infections), reduces the incidence of shunt-dependent hydrocephalus, increases the rate of discharge to home, improves quality of life at 6 months, enhances cognitive functioning at 6 months, increases the likelihood of a favourable outcome at 6 months and reduces mortality at 6 months. Outcome assessments are done by a trial nurse at the outpatient clinic 6 months after the initial bleeding, with the standard follow-up performed on the same day. The trial nurse is blinded for group allocation and does not participate in the medical treatment of the included patients. In addition, peak anti-Xa levels are measured at 12:00 on day 7 following the ictus and are readily available for analysis. A comprehensive panel of coagulation and inflammatory biomarkers is also being collected and will be analysed after completion of patient inclusion. The biomarkers include von Willebrand factor, syndecan-1, soluble thrombomodulin, tumour necrosis factor-alpha, interleukin (IL)-6, IL-8, soluble vascular cell adhesion molecule-1, angiopoietin, a disintegrin and metalloproteinase with thrombospondin motifs 13, D-dimer and coagulation factor III (also known as tissue factor). All biomarker measurements are performed on day 7 following the ictus.

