### Statistical analysis

All enrolled patients will be evaluated for the primary and secondary outcomes using an intention-to-treat analysis. To ensure the robustness of the findings, a per-protocol and as-treated analysis will also be conducted, excluding participants who do not complete follow-up, switched treatment groups, had major protocol violations and/or non-adherent patients. Baseline characteristics will be summarised by means of simple descriptive statistics. Continuous data with a parametric distribution will be presented as mean and SD, while non-parametric data will be presented as median and IQR. For between-group comparisons, independent samples t-tests or Mann-Whitney U tests will be used as appropriate. Categorical data will be presented as percentages, with the χ² test used for between-group comparisons.

The treatment effect on the primary outcome (30-day mortality) will be analysed using multivariable logistic regression, adjusting for any clinically relevant baseline imbalances if necessary. Secondary outcomes will be analysed using independent samples t-tests, Mann-Whitney U tests, χ² tests and multivariable linear and logistic regression models, as appropriate. Sensitivity analyses will also be performed, allowing early withdrawal of life support to be considered as a potential confounding variable.

All statistical uncertainty will be expressed using 95% CIs. Statistical analyses will be performed using SPSS (IBM, Armonk, New York, USA), with a significance level set at p<0.05, and all tests will be two-sided.

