## Discussion

The results of this phase II RCT will offer valuable insights into the efficacy and safety of high-dose nadroparin in patients with aSAH treated endovascularly. Our retrospective analysis suggests that high-dose LMWH may improve clinical outcomes by reducing in-hospital mortality and increasing discharge rates to home compared with standard prophylactic doses.^25^ The ISCHEMIA trial is particularly significant as it is the first to rigorously assess the impact of high-dose nadroparin in this patient population through a prospective, randomised design. Priorities of this trial are to further evaluate the clinical efficacy and safety profile of high-dose nadroparin, refine our power calculations and assess the financial and logistical feasibility of implementing this treatment regimen in the future. The additional data and revised methodologies will inform the design and implementation of a full-scale phase III trial. Given the case fatality rate associated with aSAH, we would consider an absolute mortality reduction of 5% or a relative risk reduction of at least 20% to be a clinically meaningful threshold to justify progression to a larger trial.

The anticipated benefits of high-dose nadroparin are based on its broad anti-inflammatory and immunomodulatory effects, extending beyond anticoagulation.^20 21^ By targeting key pathophysiological processes involved in DCI, such as cortical spreading depressions, endothelial dysfunction and neuroinflammation, nadroparin might mitigate secondary brain injury more effectively than current standard treatments. Given the complex and not fully understood mechanisms underlying DCI, this trial addresses an important gap in our therapeutic approach to aSAH. If proven effective, this treatment is expected to lead to improved clinical outcomes, reduced mortality and fewer SAH-related complications.

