This trial has some limitations. As a phase II RCT with a small sample size, it lacks the power to provide definitive conclusions about the effect of high-dose nadroparin on mortality and other parameters, necessitating a larger phase III RCT for confirmation. The trial is not fully blinded. We opted for an open-label approach due to both practical and ethical considerations. Nadroparin carries a risk of bleeding, and early recognition of haemorrhagic complications is essential. Unblinding in response to clinical deterioration may delay critical decisions or lead to uncertainty in management. Moreover, the dosing regimens differ between groups: patients in the intervention group receive nadroparin two times per day, while those in the control group receive it once daily. This distinction makes full blinding unfeasible, as it would likely be apparent to both patients and care providers. Additionally, nadroparin has measurable pharmacodynamic effects—such as anti-Xa levels—which would further compromise blinding, as clinicians could infer treatment allocation from laboratory results. Using a placebo control with sham anti-Xa monitoring was considered but deemed both ethically and logistically challenging. Simulating treatment would require drawing blood and performing lab tests solely to maintain blinding, offering no clinical benefit and exposing critically ill patients to unnecessary procedures. To minimise bias, a blinded trial nurse was included, and the primary outcome—mortality—was selected for its objectivity and resistance to observer bias. A further limitation of the study is that not all patients may complete all dosages due to emergency interventions requiring temporary cessation of the study medication, such as lumbar punctures or ventricular catheter placements. The heterogeneity of aSAH patients and the exclusion of those with intraparenchymal haemorrhage or non-endovascular treatments complicate the generalisation of results to the broader aSAH population or to settings preferring different aneurysm occlusion methods, such as clipping. Preferably, a larger and more diverse population will be included in future trials to establish broader applicability, if deemed safe.

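### Withdrawal of life support follows randomisation and cannot confound the comparison; a sensitivity analysis that adjusts for it may distort the treatment effect

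*Protocol article*

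**What the plan says.** The primary outcome is "mortality assessed at 30 days after the initial bleeding" (Outcomes). The Statistical analysis section analyses it by intention to treat with logistic regression, "adjusting for any clinically relevant baseline imbalances if necessary". The same section then adds: "Sensitivity analyses will also be performed, allowing early withdrawal of life support to be considered as a potential confounding variable". It does not say whether withdrawal would enter as a covariate, as an exclusion or in some other way.

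Allocation and randomisation explains where the worry comes from. In patients with high WFNS grades, "goals of care may shift toward comfort-focused measures, which can independently affect mortality outcomes regardless of the intervention". The design response is on baseline severity: "patients will undergo randomisation with stratification for World Federation of Neurosurgical Societies (WFNS) score", with the comment "Stratification by WFNS grade helps mitigate this potential source of bias". Randomisation follows consent. In the Discussion, the authors write "We opted for an open-label approach due to both practical and ethical considerations", so treating clinicians know the arm.

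**The concern.** A confounder is a common cause of treatment and outcome, or stands in for one. Withdrawal comes after allocation and cannot have caused it, so the label is wrong whatever technique is used.

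The label also points the analyst towards conditioning on something that treatment may change. Three routes are plausible from the article itself:

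- The drug is hoped to prevent complications that could prompt withdrawal (Discussion: "If proven effective, this treatment is expected to lead to improved clinical outcomes, reduced mortality and fewer SAH-related complications").
- It may cause major bleeding, a listed secondary outcome.
- In an open-label trial, knowledge of the arm may influence the decision to withdraw.

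If any of these operates, conditioning on withdrawal removes part of the effect that randomisation was meant to estimate. It can also create an association between arm and unmeasured prognosis among the patients compared. A reader could then take the adjusted figure as the cleaner answer when it is the less reliable one.

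**Working it through.** The article gives no figure for this analysis, so there is none to reproduce. The check has three parts.

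**1. Logic.** Allocation and randomisation describes the effect of comfort care on mortality as independent of the intervention. If that is true, withdrawal is unrelated to arm, does not confound, and adjustment removes no bias. If it is false, withdrawal lies between arm and death, and adjustment removes part of the effect. Neither case supports treating it as a confounder.

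**2. Expected tables.** Inputs:

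- 50 per arm (Sample size calculation).
- Control mortality 23%. This is the retrospective in-hospital rate, borrowed here for 30-day mortality.
- Treated mortality 12% (assumption).
- 50% or 70% of control deaths follow withdrawal (assumption).
- Every withdrawn patient dies by day 30 (assumption). The withdrawn stratum then says nothing about the arm effect, and the adjusted odds ratio (OR) is the OR among patients not withdrawn.

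Formulas, with d deaths and s survivors: OR = (d1/s1)/(d0/s0); SE(log OR) = √(1/d1 + 1/s1 + 1/d0 + 1/s0).

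*All deaths:* 6 of 50 v 11.5 of 50. OR = (6/44)/(11.5/38.5) = 0.457. SE = √(1/6 + 1/44 + 1/11.5 + 1/38.5) = 0.55.

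*Benefit spread evenly over both kinds of death (not-withdrawn stratum):*

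- 50%: 3 v 5.75 deaths. OR = (3/44)/(5.75/38.5) = 0.457; SE = √(1/3 + 1/44 + 1/5.75 + 1/38.5) = 0.746.
- 70%: 1.8 v 3.45 deaths. OR = 0.457; SE = 0.946.

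*All benefit through fewer withdrawals (not-withdrawn stratum):*

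- 50%: 5.75 v 5.75 deaths. OR = 38.5/44 = 0.875. Withdrawal deaths must fall from 5.75 to 6 − 5.75 = 0.25, a 96% drop.
- 70%: 3.45 v 3.45 deaths. OR = 0.875. Withdrawal deaths must fall from 8.05 to 6 − 3.45 = 2.55, a 68% drop.

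*No treatment effect (23% in both arms):* OR = 1 with or without adjustment. SE rises from √(2/11.5 + 2/38.5) = 0.48 to √(2/5.75 + 2/38.5) = 0.63 at 50%, or √(2/3.45 + 2/38.5) = 0.79 at 70%. Precision is lost and no bias is removed.

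**3. Simulation of the pathway.** There were 2,000,000 patients per scenario, and every parameter is an assumption. U is an unmeasured standard normal prognostic factor and T the arm.

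- Deterioration D: logit = −1.0 + 1.0U + aT.
- Withdrawal: logit = −4.5 + 2.5D + 0.8U + bT.
- Death: probability 0.97 if withdrawn; otherwise logit = −3.2 + 1.2D + 0.8U + cT.

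Control mortality comes out at about 14% and control withdrawal at about 7%.

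| Scenario | a, b, c | Total OR | OR adjusted for withdrawal | OR excluding withdrawn |
|---|---|---|---|---|
| Benefit through less deterioration | −1.0, 0, 0 | 0.72 | 0.82 | 0.81 |
| Arm changes withdrawal only | 0, −0.8, 0 | 0.80 | 1.07 | 1.07 |
| Both | −1.0, −0.8, 0 | 0.60 | 0.86 | 0.86 |
| Harm through more deterioration | 1.0, 0, 0 | 1.35 | 1.24 | 1.25 |
| Strong benefit with a direct effect | −1.5, 0, −0.5 | 0.48 | 0.48 | 0.47 |
| No effect | 0, 0, 0 | 1.00 | 1.00 | 1.00 |

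Benefit and harm can both be diluted, and the direction can reverse when withdrawal is the only route. In two scenarios the OR barely moves. Covariate adjustment and exclusion behave almost alike, so the unnamed technique matters little.

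**The case against.** The strongest reply is that this is one sentence about a sensitivity analysis in a condensed article. The primary model takes baseline covariates only and counts every death, and the technique may be specified in a document not shown. Early withdrawal may mostly reflect admission severity: the article links it to high WFNS grades and places delayed cerebral ischaemia at days 4 to 10, so some withdrawals may precede any drug action. On that view withdrawal need not be a mediator.

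Much of this stands. It limits the consequences and rules out an unconditional claim of bias. The shift to 0.88 is an extreme case: it needs withdrawal deaths to fall by 68-96% with no effect on other deaths. The wish to examine withdrawal in an open-label mortality trial is also legitimate.

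It does not rescue the label. A withdrawal driven purely by admission severity is balanced in expectation by randomisation, and the way to address chance imbalance is to adjust for the severity measure itself. No unseen detail can turn a post-randomisation event into a cause of the allocation.

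A reader might infer that the trial's main result is biased, or that adjusting necessarily biases the effect. The article supports neither: withdrawal does not enter the primary model, and the distortion depends on treatment affecting withdrawal or its causes.

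**Conclusion.** The point holds as a should-fix. The sentence calls a post-randomisation event on the way to death a possible confounder, which it cannot be. Acting on that label can dilute or distort a real effect if treatment influences withdrawal or its causes; otherwise it removes no bias and can cost precision. Size and direction cannot be determined from the article. On the assumed rates, the OR lies between 0.46 with a larger SE (0.75-0.95 instead of 0.55) and 0.88 in the extreme case.

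A reader might also infer that the decision on a phase III trial is at risk, because the Discussion sets a threshold of a 5% absolute or 20% relative mortality reduction. In the extreme illustration, all-cause mortality clears both (23 − 12 = 11 points; 11/23 = 48%). Patients not withdrawn clear neither: 5.75/44.25 − 5.75/49.75 = 1.4 points, or 11% relative, at 50%; 3.45/41.95 − 3.45/47.45 = 1.0 point, or 12%, at 70%. But the article does not say that this sensitivity analysis feeds the decision, so the comparison shows only why the result should not be read as a corrected estimate.

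**What to change.** In the Statistical analysis section, remove withdrawal of life support as an adjustment covariate or ground for exclusion, and stop describing it as a confounder. In its place:

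- Report by arm the 30-day deaths with and without prior withdrawal of life support, with 95% confidence intervals, and the timing of and reason for withdrawal where recorded. Label this as a descriptive analysis of a post-randomisation event.
- If the tendency to withdraw is to be addressed by covariate adjustment, use baseline variables only, such as WFNS grade and age.

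The primary analysis needs no change. The cost is a change of wording before analysis, plus one check: withdrawal status, timing and reason must be in the collected data. The planned analysis implies that status is recorded, but the article does not state it, and timing or reason could need extra case report form fields.

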### Data safety analysis

Adverse events (AEs) and serious AEs (SAEs) will be recorded in our electronic case report form (CRF). Only AEs occurring during hospital admission that are unrelated to the SAH must be reported to the institutional review board and principal investigator. All SAEs will be reported without undue delay after obtaining knowledge of the events. In this trial, certain SAEs are anticipated in patients with SAH, including severe hyponatraemia (serum sodium <125 mmol/L), hypokalaemia (serum potassium <3.5 mmol/L), fever, hydrocephalus, DCI, periprocedural aneurysm rupture, rebleed, delirium, Terson’s syndrome, epilepsy, diffuse parenchymal swelling, nosocomial meningitis, pneumonia and urinary tract infection. These expected SAEs will be recorded in the CRF and do not require further reporting.

A data and safety monitoring board (DSMB) is installed for this trial including a neurologist, neurosurgeon and independent statistician. The members are not involved in the trial and have no competing interests. Their tasks, responsibilities and working procedures are outlined in a charter. The DSMB will review safety data and the incidence of (S)AEs at three specified intervals: After 30, 60 and 100 patients have completed their 30-day follow-up. The DSMB will conduct ongoing safety surveillance, particularly regarding the occurrence of SAEs related to an increased risk of haemorrhagic complications. Additionally, the DSMB will advise on the continuation of the trial and may recommend the Steering Committee of the ISCHEMIA trial to terminate the trial if there is clear and substantial evidence of harm. No interim analysis is planned in this trial.

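### Rebleed and Terson's syndrome are exempt from SAE reporting beyond the CRF in a trial of a higher anticoagulant dose, and rebleeding is listed as an expected benefit although it can also count as a bleeding harm

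*Protocol article*

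**What the plan says.** The Data safety analysis section of the protocol article opens with a general rule: "All SAEs will be reported without undue delay after obtaining knowledge of the events". It then lists SAEs that are anticipated in this disease. Part of the list reads "hydrocephalus, DCI, periprocedural aneurysm rupture, rebleed, delirium, Terson’s syndrome, epilepsy, diffuse parenchymal swelling". For everything on the list the rule is: "These expected SAEs will be recorded in the CRF and do not require further reporting".

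The same section describes a DSMB that reviews safety data and (S)AE incidence once 30, 60 and 100 patients have completed 30 days. Between reviews it is to keep a continuing watch, "particularly regarding the occurrence of SAEs related to an increased risk of haemorrhagic complications". Its working procedures are left to a charter. No interim analysis is planned.

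The Outcomes section bears on the same events in two ways:

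- Major bleeding is a secondary outcome that the treatment may increase. It covers fatal bleeding and "symptomatic bleeding in critical areas or organs (such as intracranial, intraspinal, intraocular" and further sites. Non-major bleeding covers every other reported bleed.
- A separate objective is whether the treatment "reduces other SAH-related complications (such as severe hyponatraemia, postprocedural aneurysm rupture, rebleeding, delirium, epilepsy" and other events.

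The limitations part of the Discussion defends the open-label design partly because nadroparin can cause bleeding and bleeding complications need to be recognised early.

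**The concern.** Exempting events that belong to the disease keeps reporting manageable, and it is reasonable for events such as fever or hyponatraemia. A rebleed is different. It is expected after a subarachnoid haemorrhage, but it is also an event that a higher anticoagulant dose could plausibly make more frequent or more severe. Terson's syndrome, as an intraocular bleed, belongs with it. Being expected in the disease does not make an event uninformative about the drug.

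The exemption therefore covers events of the kind the DSMB is asked to watch most closely. The adverse-event rule offers no other route, because mandatory reporting of in-hospital AEs is limited to those unrelated to the SAH, and a rebleed is easily classed as related. The article describes no way for an exempt rebleed to reach the DSMB between reviews.

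The Outcomes section adds a second difficulty. A symptomatic rebleed counts towards an outcome expected to rise with treatment and is also named among complications expected to fall. A reader of the results could not tell which way the trial regards an excess.

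At stake is the protection of participants during the trial and the clarity of the safety report. The primary analysis of 30-day mortality is not affected.

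**Working it through.** The article gives no figure to reproduce on this point. The check sets the statements side by side and then works out the timing.

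**Side by side**

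| Event | Data safety analysis | Outcomes: harm direction | Outcomes: benefit direction |
|---|---|---|---|
| Rebleed | Exempt, CRF only | Major bleeding if fatal or symptomatic intracranial; otherwise non-major bleeding if reported | Named as a complication to be reduced |
| Terson's syndrome | Exempt, CRF only | Major bleeding if symptomatic (intraocular) | Not named in the list |
| Aneurysm rupture | *Periprocedural* rupture exempt | Major bleeding if it causes fatal or symptomatic intracranial bleeding | *Postprocedural* rupture named |

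Only rebleeding is shown both on the exempt list and on the benefit list. The two rupture terms differ. The Interventions section gives the high dose only once the aneurysm is secured, so a rupture during coiling comes before that treatment.

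**Timing, if exempt events reached the DSMB only at scheduled reviews**

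Inputs: reviews after 30, 60 and 100 patients with 30 days of follow-up (Data safety analysis); 25 to 50 eligible patients per year (Sample size calculation). The planned 100 patients within 4 years (Study design and setting) means 100/4 = 25 per year, the slow end of that range. The fast end assumes that every eligible patient is enrolled.

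Months from first enrolment = 12 × n / rate + 1.

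| Review | 50 per year | 25 per year |
|---|---|---|
| 30 patients | 7.2 + 1 = 8.2 | 14.4 + 1 = 15.4 |
| 60 patients | 14.4 + 1 = 15.4 | 28.8 + 1 = 29.8 |
| 100 patients | 24.0 + 1 = 25.0 | 48.0 + 1 = 49.0 |

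The gap between the second and third reviews is 25.0 − 15.4 = 9.6 months at 50 per year and 49.0 − 29.8 = 19.2 months at 25 per year. High-dose treatment ends by day 21 after the bleed, and the third review follows 30 days of follow-up in all 100 patients. That review therefore cannot change high-dose treatment for anyone in the trial.

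**Could such events occur before the first review?**

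With 1:1 allocation, about 30/2 = 15 of those 30 patients would be in the high-dose arm. The article gives no rebleed rate, so the rates p below are assumptions. P(at least one) = 1 − (1 − p)^15.

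| Assumed rebleed rate | Chance of at least one among 15 |
|---|---|
| 1% | 14% |
| 2% | 26% |
| 5% | 54% |
| 10% | 79% |

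Over this range, an exempt rebleed in the high-dose arm before the first review runs from unlikely to probable.

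**The case against.** The strongest reply is that nothing is lost. Exempt events are still entered in the CRF, the DSMB sees (S)AE incidence at three reviews, and continuing surveillance of haemorrhagic SAEs is stated. The route between reviews is the sort of detail that a condensed article leaves to the charter or full protocol. A general rule followed by a listed exception is also a common form and need not be a contradiction.

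Much of this stands. The general rule and the exemption can be read together, and late detection cannot be claimed as fact. What remains is that the article does more than stay silent. It states that no further reporting is required for these events, and that statement is hard to square with the surveillance task and the stated need for early recognition. An unseen charter may supply a route, but the published rule would still need correcting.

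Four stronger readings are tempting and are not supported:

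- *Bleeding harm will be diluted.* This needs a pooled endpoint of SAH-related complications. Neither Outcomes nor Statistical analysis defines one.
- *Rebleeds are misfiled, so harm is hidden.* Major and non-major bleeding are separate outcomes and between them cover reported rebleeds. All tests are two-sided, so listing rebleeding as a benefit does not stop an excess from being tested.
- *Aneurysm rupture is on both lists.* The terms differ, as shown in the table.
- *The small arms show the size of the defect.* With 0 events in 50, the exact 95% upper bound is 1 − 0.025^(1/50) = 7.1%. That reflects the sample size and would be the same under any reporting rule.

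**Conclusion.** The point holds in a limited form. In a trial of a higher anticoagulant dose, rebleed and Terson's syndrome should not be exempt from SAE reporting beyond the CRF. The exemption sits badly with the DSMB's surveillance task, with the major-bleeding outcome and with the article's own argument for early recognition. Rebleeding is also given two opposite expected directions within the Outcomes section.

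The possible delay is about 8 to 15 months from first enrolment to the first scheduled review, and about 10 to 19 months between the second and third. These figures assume steady enrolment at 25 to 50 patients per year and no flow of exempt events to the DSMB between reviews. The second assumption cannot be checked without the charter, so the delay is a risk and not an established fact. The opposite directions are a defect of clarity and do not invalidate any planned test.

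**What to change.** In Data safety analysis, remove rebleed, Terson's syndrome and any other haemorrhage after the start of study drug from the exempt list. State that they are reported as SAEs and passed to the DSMB by arm as they occur. If the charter already provides that route, say so and bring the exemption into line with it.

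In Outcomes, report rebleeding with the bleeding (harm) outcomes and take it out of the complications that treatment is expected to reduce. Reconcile *periprocedural* aneurysm rupture in Data safety analysis with *postprocedural* aneurysm rupture in Outcomes, so that it is clear whether one event or two are meant and which can follow study drug.

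The cost is a short amendment to two sections and a few extra SAE reports. Sample size, randomisation and the primary analysis do not change.
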